### Analyses

Data will be analyzed on an intention-to-treat basis, using random effects mixed modeling to examine group differences in the outcome measures among baseline, post-intervention and follow-up. Linear analyses will be used to examine the potential mediation of the five identified protective factors (see Figure 2). We will calculate the (a) direct effect of the program on the outcome measures (τ); (b) effect of the intervention on each of the mediating variables, adjusted for baseline values (α); (c) the effect of the residual change score (post intervention score adjusted for the baseline score) of the proposed mediating variables on the outcome measures, after adjustment for the intervention (β); and then examine whether there is attenuation or change in significance in the relationship between the intervention and the outcome measures, after adjustment for the change in the mediating variables (τ'). The product of the α and β coefficients will be used to provide an estimate of the magnitude of the mediation effect in the units of the outcome variable, and the 95% confidence intervals of the point estimates of the mediated effects will be examined to test for mediation [41].

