## Discussion

Little work has been done to evaluate the effectiveness of resilience training with adults in the general population. We are not aware of any studies that have used resilience training to reduce psychosocial and physical indicators of CHD risk, or that have assessed the added value of physical activity promotion. This paper describes the design and methods of a trial of the *READY *psychosocial resilience training program, which will provide data on each of these issues. This study is consistent with positive psychology which focuses on the strengths of individuals that enables them to thrive, and the call for prevention and health promotion research to integrate psychosocial (e.g., depression) and behavioral (e.g., physical activity) risk factors [42].

This study is innovative in a number of ways. Unlike cross sectional studies that assess the concurrence of personal characteristics and resilience, this is an intervention study of resilience *training*. The program targets otherwise healthy adults in the general population rather than children or adults in specific adverse circumstances. This is a novel application of resilience training; to promote heart health by focusing on identified CHD risk factors of depression, poor social support and life stress. Subsequently, the assessment framework incorporates indicators of both psychosocial (well-being, depression) and physical (blood pressure, lipids, blood glucose) health. As it is a protective factor for both heart health and psychosocial well-being, we have integrated physical activity promotion with the resilience program, and will examine the added value of doing so.

At a conceptual level, this study will contribute to our understanding of resilience. The mediational analyses will allow us to evaluate our model of resilience that targets five protective factors (positive emotions, cognitive flexibility, life meaning, active coping, social support) to promote psychosocial well-being (ie., conceptual theory test), and the independent contribution of each of the protective factors in promoting change. We will also be able to evaluate the extent to which the *READY *program impacts on each of these protective factors as hypothesized mechanisms of change (i.e., action theory test).

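### The β and τ′ mediation models omit the outcome's own baseline score, which can inflate false findings of mediation for related self-report scales

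*Protocol article*

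**What the plan says.** The Analyses section of the protocol article sets out the mediation analysis step by step and gives an adjustment for three of its quantities:

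- **α:** "effect of the intervention on each of the mediating variables, adjusted for baseline values (α").
- **β:** "c) the effect of the residual change score (post intervention score adjusted for the baseline score) of the proposed mediating variables on the outcome measures", with the adjustment given as "on the outcome measures, after adjustment for the intervention (β").
- **τ′:** the intervention effect "after adjustment for the change in the mediating variables (τ"′).

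For τ no covariate is named. The inference follows from these: "The product of the α and β coefficients will be used to provide an estimate of the magnitude of the mediation effect", and the 95% confidence interval of that product is the test.

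The mediator's baseline therefore enters at α and in the residual change score used for β. The outcome's baseline is named at no mediation step. It is collected: the Measures section puts the questionnaires at baseline, and the randomization section places allocation after the baseline assessment. Baseline outcome data are used only in the separate mixed model for group differences.

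**The concern.** Randomization protects α. It does not protect β, because within an arm nobody is randomized to a level of the mediator. Any stable characteristic that lifts both scales enters β unless it is adjusted away.

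The plan tries to deal with this by residualizing the mediator on its own baseline. That works only in part. A single baseline score reflects the stable level plus occasion noise, so some of the stable level stays in the residual. The post-intervention outcome, with no baseline adjustment, carries its stable level in full. The two then correlate even if changing the mediator does nothing.

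Mediators and primary outcomes here are closely related self-reports from one battery. The Background itself says that each protective factor has been related to lower depressive symptoms. The Discussion intends to use the mediation results to judge what each factor separately contributes to change, and that claim rests on β. A factor could be credited as a mechanism because people with a better stable level score better on both scales.

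**Working it through.** **The plan's own figure.** The mediation section gives no number. The Sample Size section gives a 3.0-point difference, SD 4.0, two-sided 0.05 and 80% power: n = 2 × (1.960 + 0.842)² × 4.0² / 3.0² = 2 × 7.85 × 1.778 = 27.9, so 28 per group. This reproduces. It also supplies a plausible effect, 3.0/4.0 = 0.75 SD, used below as the program's shift of the mediator. Recruitment is 30-35 per condition, so 32 per arm is used alongside 28.

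**Assumptions, none given in the article.** All scores have unit variance. A share r of each score is stable trait and 1 − r is independent occasion noise. The mediator and outcome traits correlate ρ (the sign follows the scale's direction). The true mediator-to-outcome effect and the program effect on the outcome are both zero. Clustering is ignored.

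**Population β as written.** Within arm, the residual change is R = M1 − r·M0.

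- Cov(R, Y1) = ρr − r·ρr = ρr(1 − r)
- Var(R) = 1 − r²
- β = ρr(1 − r)/(1 − r²) = ρr/(1 + r)

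**Population β with baseline outcome Y0 added.** Cov(R, Y0) = ρr(1 − r) and Cov(Y0, Y1) = r, so

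- β = ρr(1 − r) / [(1 + r) − ρ²r²(1 − r)]

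For example, with r = ρ = 0.7, as written: 0.49/1.7 = 0.29. With Y0: 0.147/(1.7 − 0.072) = 0.09. The true value is 0.

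| r | ρ | β as written | β with Y0 |
|---|---|---|---|
| 0.5 | 1 / 0.7 / 0.5 | 0.33 / 0.23 / 0.17 | 0.18 / 0.12 / 0.09 |
| 0.6 | 1 / 0.7 / 0.5 | 0.38 / 0.26 / 0.19 | 0.17 / 0.11 / 0.08 |
| 0.7 | 1 / 0.7 / 0.5 | 0.41 / 0.29 / 0.21 | 0.14 / 0.09 / 0.06 |

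**False mediation rate.** In simulated trials, α came from M1 on intervention and M0. β came from Y1 on intervention and R, with or without Y0. The table shows the percentage of trials in which the 95% interval for αβ excluded zero, for ρ = 1 / 0.7 / 0.5.

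| Setting | Interval | As written | With Y0 |
|---|---|---|---|
| 32 per arm, r = 0.6 | Monte Carlo | 68 / 38 / 20 | 21 / 12 / 9 |
| 32 per arm, r = 0.6 | normal-theory | 49 / 23 / 11 | 12 / 7 / 4 |
| 28 per arm, r = 0.7 | normal-theory | 43 / 19 / 10 | 9 / 5 / 3.5 |

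Varying r over 0.5-0.7 at 32 per arm gives 18-68% as written and 8-26% with Y0 (Monte Carlo). Pooling the two active arms against the wait list (84 participants, r = ρ = 0.7, normal-theory) gives 36% as written and 8% with Y0.

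**Controls.** With ρ = 0 the rate is about 5% or less (3% with the normal-theory interval), so the excess comes from the shared trait. With ρ = 0.3 it is about 5-10%, depending on the interval.

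**The case against.** The strongest reply is that the article does not close the covariate list. Saying that β is adjusted for the intervention separates it from a crude association; the text does not say that nothing else is included. Nor does it say whether the outcome in these steps is a raw post score, and Figure 2, which shows the mediation model, is not available here. If the outcome were change from baseline, false mediation would fall to 4-6% under the same assumptions.

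Part of this stands: the full plan may contain the covariate. But the article spells out baseline adjustment on the mediator side and names only the intervention on the outcome side. It uses residual change for the mediators and never describes the outcome as a change score. Someone following the text would fit the model examined above. If the full plan differs, the article misdescribes it and needs the same correction.

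Several stronger readings are tempting and are not supported:

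- **The test will declare mediation whenever the mediator is inert.** It will not. The error rate is inflated, and a false finding also needs the program to move the mediator.
- **The bias affects all outcomes alike.** Lipids, glucose, blood pressure and step counts are unlikely to share a strong trait with a questionnaire mediator.
- **The highest rates are typical.** Values near 70% need mediator and outcome to share one identical trait (ρ = 1) and the Monte Carlo interval. The article names no interval method.
- **The Discussion's claim to assess "the extent to which the *READY *program impacts on each of these protective factors as hypothesized mechanisms of change" is undermined.** That sentence concerns α, which randomization protects. The affected claim is the one about each factor's separate contribution to change.

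**Conclusion.** The point holds as a bias in β, and hence in αβ and τ′, for self-report outcomes related to the mediators. Under stable shares of 0.5-0.7, trait correlations of 0.5-1 and a 0.75 SD shift in the mediator, false mediation is roughly 10-50% with a normal-theory interval and 20-70% with a Monte Carlo interval. With the outcome's baseline added, it is roughly 4-12% and 8-26%.

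The direction of the bias follows from the algebra whenever the traits correlate and the baseline mediator score is imperfect. The size rests on assumed values that the article does not give, and on ignoring clustering. The mixed-model comparison of groups and the sample size are not affected, so this is a should-fix matter for the mechanism analysis only.

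**What to change.** In the Analyses section, add the baseline score of the outcome as a covariate in the τ, β and τ′ models, next to the terms already named. State in the same place that residual mediator-outcome confounding cannot be excluded, so that the Discussion's claims about mechanism are read with that limit.

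The cost is one degree of freedom. For a 28 v 28 comparison, the β model goes from 56 − 3 = 53 to 52 residual degrees of freedom. No new data are needed, because the score is collected before allocation. The change reduces the bias but does not remove it: at r = ρ = 0.7, β falls from 0.29 to 0.09, not to 0.

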## Discussion

Little work has been done to evaluate the effectiveness of resilience training with adults in the general population. We are not aware of any studies that have used resilience training to reduce psychosocial and physical indicators of CHD risk, or that have assessed the added value of physical activity promotion. This paper describes the design and methods of a trial of the *READY *psychosocial resilience training program, which will provide data on each of these issues. This study is consistent with positive psychology which focuses on the strengths of individuals that enables them to thrive, and the call for prevention and health promotion research to integrate psychosocial (e.g., depression) and behavioral (e.g., physical activity) risk factors [42].

This study is innovative in a number of ways. Unlike cross sectional studies that assess the concurrence of personal characteristics and resilience, this is an intervention study of resilience *training*. The program targets otherwise healthy adults in the general population rather than children or adults in specific adverse circumstances. This is a novel application of resilience training; to promote heart health by focusing on identified CHD risk factors of depression, poor social support and life stress. Subsequently, the assessment framework incorporates indicators of both psychosocial (well-being, depression) and physical (blood pressure, lipids, blood glucose) health. As it is a protective factor for both heart health and psychosocial well-being, we have integrated physical activity promotion with the resilience program, and will examine the added value of doing so.

At a conceptual level, this study will contribute to our understanding of resilience. The mediational analyses will allow us to evaluate our model of resilience that targets five protective factors (positive emotions, cognitive flexibility, life meaning, active coping, social support) to promote psychosocial well-being (ie., conceptual theory test), and the independent contribution of each of the protective factors in promoting change. We will also be able to evaluate the extent to which the *READY *program impacts on each of these protective factors as hypothesized mechanisms of change (i.e., action theory test).

There are some methodological issues to consider with this study. Recruitment of staff from a regional district of a government department may result in a study sample that is not representative of the general population. As participants will be recruited from within one organization, there may be a risk of contamination between intervention conditions if they communicate with each other. However the clustering of individuals by occupational group and geographical location may reduce this risk. Participants receiving the physical activity promotion will receive one more intervention session than those who receive only the psychosocial resilience training. It is unlikely however, that the additional two and a half hour session, in the context of the 25 hour program, will by itself provide marked additional benefits. To minimize potential trainer effects, interventionists will be involved in both group conditions (i.e. resilience training AND resilience training + physical activity promotion).

## Conclusion

If effective, the *READY *program will demonstrate an innovative means to improve psychosocial well-being and thereby promote heart health in adults in the general population. We will also be able to assess the added value of integrating physical activity promotion and resilience training. If the program is effective, it could be disseminated through similar training programs in worksites or community settings, or adapted to use written or web-based self-help materials. The program could also be used to promote psychosocial well-being in any population subgroups identified as at risk of depression, poor social support and life stress.

## Abbreviations

CHD: Coronary Heart Disease.
